# A single-center, randomized, non-inferiority study evaluating seroma formation after mastectomy combined with flap fixation with or without suction drainage: protocol for the *S*eroma reduction and dr*A*in f*R*ee m*A*stectomy (SARA) trial

**DOI:** 10.1186/s12885-020-07242-0

**Published:** 2020-08-07

**Keywords:** Mastectomy, Seroma, Drain free, Flap fixation

## Abstract

**Background:**

Seroma formation is a common complication after breast cancer surgery and can lead to delayed wound healing, infection, patient discomfort and repeated visits to the outpatient clinic. Mastectomy combined with flap fixation is becoming standard practice and is currently combined with closed-suction drainage. There is evidence showing that closed-suction drainage may be insufficient in preventing seroma formation. There is reasonable doubt whether there is still place for closed-suction drainage after mastectomy when flap fixation is performed.

We hypothesize that mastectomy combined with flap fixation and closed suction drainage does not cause a significant lower incidence of seroma aspirations, when compared to mastectomy and flap fixation alone. Furthermore, we expect that patients without drainage will experience significantly less discomfort and comparable rates of surgical site infections.

**Methods:**

This is a randomized controlled trial in female breast cancer patients undergoing mastectomy and flap fixation using sutures with or without sentinel lymph node biopsy (SLNB). Patients will be eligible for inclusion if they are older than 18 years, have an indication for mastectomy with or without sentinel procedure. Exclusion criteria are modified radical mastectomy, direct breast reconstruction, previous history of radiation therapy of the unilateral breast, breast conserving therapy and inability to give informed consent. A total of 250 patients will be randomly allocated to one of two groups: mastectomy combined with flap fixation and closed-suction drainage or mastectomy combined with flap fixation without drainage. Follow-up will be conducted up to six months postoperatively. The primary outcome is the proportion of patients undergoing one or more seroma aspirations. Secondary outcome measures consist of the number of invasive interventions, surgical site infection, quality of life measured using the SF-12 Health Survey, cosmesis, pain and number of additional outpatient department visits.

**Discussion:**

To our knowledge, no randomized controlled trial has been conducted comparing flap fixation with and without closed-suction drainage with seroma aspiration as the primary outcome. This study could result in finding evidence that supports performing mastectomy without closed-suction drainage.

**Trial registration:**

This trial was approved by the medical ethical committee of Zuyderland Medical Center METC-Z on 20 March 2019 (METCZ20190023). The SARA Trial was registered at ClinicalTrials.gov as per July 2019, Identifier: NCT04035590.

## Background

Seroma formation can be a bothersome complication after breast cancer surgery and is often considered to be an inevitable consequence of mastectomy [1–4]. Seroma can lead to delayed wound healing, infection, skin flap necrosis, patient discomfort and repeated visits to the outpatient clinic. Therefore, extensive research has focused on the pathophysiology to be able to better prevent seroma. Seroma is a collection of serous fluid containing blood plasma and/or lymph fluid and a key element in the prevention seems the obliteration of dead space [4–8]. However, controversy exists about the best technique to achieve this goal. A recent systematic review of flap fixation techniques in reducing seroma formation and its sequelae after mastectomy by van Bastelaar et al. (2018) showed that flap fixation reduces seroma formation and seroma aspiration after mastectomy with or without axillary clearance [9]. Flap fixation with tissue glue appears to yield similar results when compared to flap fixation using sutures [10]. This conclusion is supported by an interim analysis of a trial by Granzier et al. (2019), showing that flap fixation with either sutures or adhesive tissue glue reduces the number of needle aspirations compared to patients undergoing simple wound closure [11]. Other studies on flap fixation also show promising results in reducing the incidence of seroma and seroma aspirations after breast cancer surgery [12–18]. Mastectomy combined with flap fixation is becoming standard practice, and is currently still combined with closed-suction drainage.

For many years closed suction drainage was considered the most effective intervention for reducing seroma formation after breast cancer surgery. This practice was supported by trials showing that mastectomy without the use of drains was associated with a higher occurrence of seroma and greater volumes of seroma in the post-operative period [19–23]. Other studies in drain free mastectomy have shown that application of suction drainage does not prevent seroma formation and that there is no significant difference between the incidence of seroma formation [24–26]. These studies also concluded that closed suction drainage is associated with a longer postoperative hospital stay on average, and that a long duration of drainage was related to a higher incidence of seroma formation [27–29]. The question therefore is if there is still a place for closed-suction drainage after mastectomy with flap fixation, as this has shown to decrease seroma formation [21, 22]. However, the evidence consists of only small case series and a large randomized controlled trial is needed to provide definitive proof.

To our knowledge, no randomized controlled trial has been conducted comparing flap fixation with and without the use of closed-suction drainage using seroma aspirations as the primary outcome. The SPIRIT Statement guidelines were used for designing and describing this trial [30, 31].

## Objectives

### Research hypothesis

We hypothesize that flap fixation with closed suction drainage does not cause a significantly lower incidence of seroma aspirations when compared to flap fixation alone. We also expect that patients without drainage will experience less discomfort and will have comparable rates of surgical site infections.

### Study objectives

#### Primary objective

To evaluate whether omitting drains after mastectomy in combination with flap fixation does not lead to a higher incidence of seroma formation and seroma aspirations in women with invasive breast cancer or ductal carcinoma in situ (DCIS).

#### Secondary objectives

Assess whether patients with or without drainage after mastectomy experience more pain, experience different quality of life, undergo more invasive interventions related to seroma, develop more surgical site infections or require more unplanned visits to the hospital. Self-assessed cosmesis will also be evaluated.

## Methods/design

### Study design

The SARA (Seroma reduction and drAin fRee mAstectomy) trial is a single center randomized controlled trial. As it is obvious whether or not a drain is used, no blinding can be performed. Patients will be allocated to one of two groups. One group will undergo mastectomy combined with flap fixation and placement of low vacuum drainage and the other group will undergo mastectomy with flap fixation without placement of low vacuum drainage. In both groups the same method for flap fixation will be applied. Flap fixation will be achieved using sutures [10].

### Setting

This single center randomized controlled non-inferiority trial will be conducted in a Dutch teaching hospital in the south of the Netherlands, the Zuyderland Medical Center. Roughly 500 patients are treated for breast cancer annually. All patients will be recruited from the surgical breast cancer clinic (Borstcentrum Zuyd) after evaluation for invasive breast cancer or DCIS (ductal carcinoma in situ).

### Eligibility criteria

#### Inclusion criteria

Patients are eligible for inclusion if they meet the following requirements: (1) patients with an indication for mastectomy with or without sentinel lymph node biopsy (SLNB) suffering from invasive breast cancer or DCIS, (2) female gender, (3) older than 18 years.

#### Exclusion criteria

The exclusion criteria are as follows: (1) patients undergoing modified radical mastectomy, (2) patients undergoing breast conserving therapy, (3) patients undergoing direct breast reconstruction, (4) patients with a history of radiation therapy of the unilateral breast, (5) patients unable to comprehend implications and extent of the study and therefore unable to sign for informed consent.

### Recruitment

The trial is planned to start inclusion in January 2020. Patients will be screened in the outpatient department by one of the breast surgeons. If they meet inclusion and exclusion criteria they will be informed about the trial and will be given a week to decide whether or not they want to participate. If so, written informed consent will be obtained.

### Study interventions

The operative procedure will be performed by one of four experienced breast surgeons. Dissection of the breast tissue including the prepectoral fascia is performed using electrocautery. After performing the mastectomy the extent of the skin flaps will be measured in centimeters from medial to lateral and from cranial to caudal. Wound surface is assumed to be elliptical and will be calculated using the formula A = a x b x π, see Fig. 1. The skin flaps will be sutured on to the pectoral muscle using polyfilament absorbable sutures (Vicryl 3.0), placed at 4–5 cm intervals in two or three rows, depending on the extent of the skin flaps. The distance between all sutures will be 4–5 cm. The fat of the subcutis of the skin flaps will be sutured on to the pectoral muscle. This will be performed as tension free as possible minimizing the risk of dimpling in the skin. The axillary area is not approximated using sutures. The skin edges will be sutured in one layer using absorbable monofilament sutures (Moncryl 3.0 or V-loc 30 cm), depending on the surgeon’s preference. Depending on randomization, a low suction drain will be placed before wound closure (Armstrong medical).

**Fig. 1 Fig1:**
[figure not shown]
Formula to calculate wound surface

### Mastectomy with low vacuum drainage

In the group with closed suction drainage, one low vacuum drain will be placed in the mastectomy gutter, lateral to the pectoral muscle before flap fixation is performed. The drain is connected to a low suction drain bottle. Drain output will be recorded daily. Drain removal will be performed once daily output is below 50 mL or after a maximum of 48 h, irrespective of drain output.

### Mastectomy without low vacuum drainage

In the group without closed suction drainage the procedure is performed as described in ‘Study interventions’ and placement of drains is omitted.

### Study outcomes

#### Primary outcome measure

The primary outcome is the percentage of patients undergoing seroma aspiration of clinically significant seroma during the first 6 months post-operatively. Clinically significant seroma is defined as:

a. Wound healing is at risk due to seroma (wound dehiscence, seroma leakage, necrosis).

b. There is discomfort or pain caused by large amounts of seroma, characterized by tenseness of the skin.

c. There is contaminated or infected seroma and aspiration is necessary to treat infection. All patients that undergo seroma aspiration due to infection will also be treated with a 1 week course of Augmentin 625 mg 3 times daily.

Seroma presents itself in many forms, ranging from minimal seromas to high volume seromas. It is important to realize that not every seroma is a clinically significant seroma. By defining the primary outcome as stated above, we find this to be the most objective assessment of clinically significant seroma as this is defined by clinical relevance. By clearly stating the definition of the primary endpoint, we hope to avoid misinterpretation and deviation from the study protocol. This creates uniformity in deciding whether seroma needs to be aspirated, which is of crucial importance for assessing the primary endpoint.

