#### Secondary outcome measures

Assess:
Number of invasive interventions related to seroma or wound healing defined as: every aspiration of clinically significant seroma, incision and drainage of abscess or infected seroma and/or operative debridement of the wound.Surgical site infection (SSI) rate, defined as redness, pain, heat or swelling at the site of the incision or by the drainage of pus. Infection rate will be measured by A) the need for antibiotics, B) seroma aspiration due to infection or C) surgical drainage.Cosmesis assessed by the patient at every planned outpatient clinic visit. At these visits patients are asked to rate the cosmesis of the chest wall using a numeric rating scale (NRS) on a scale from 0 to 10.Quality of life measured using the SF-12 (Short Form) Health Survey. This is a 12-item questionnaire used to assess health related quality of life from the patient’s perspective. Two subscales are derived from the SF-12: the Physical Component Summary (PCS) and the Mental Component Summary (MCS) with a range from 0 to 100. A score of less than 50 means the patient scores lower than the general population and a score of more than 50 means the patient scores higher than the general population. Patients will be asked at baseline and at every postoperative planned outpatient clinic visit to fill in this questionnaire.The number of outpatient department visits, measured during the first 6 months postoperatively. This will be measured to see if patients have to come to the hospital more often due to seroma or seroma related complications.Wound pain and pain at the drain site measured by the patient using the NRS on a scale from 0 to 10 at the first postoperative outpatient clinic visit.

All outcome measures will be measured during the first 6 months postoperatively.

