#### Primary study parameter(s)

The upper bound of the confidence interval of the difference in proportion of patients that received one or more seroma aspirations during the first 6 months post-operatively will be compared to the non-inferiority limit of 10%. In case the upper bound is below the non-inferiority limit, non-inferiority will be concluded. For the primary non-inferiority hypothesis, we will perform a per protocol analysis and an intention to treat analysis as sensitivity analysis.

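### The needle-only primary endpoint scores surgical drainage without aspiration as a non-event, and the analysis sentence drops the endpoint's clinical-significance condition

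*Protocol article*

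**What the plan says.** The protocol article describes the primary endpoint in several places.

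- **Primary outcome measure:** "The primary outcome is the percentage of patients undergoing seroma aspiration of clinically significant seroma during the first 6 months post-operatively". Three criteria, a to c, define clinical significance. Criterion c covers infection in these words: "There is contaminated or infected seroma and aspiration is necessary to treat infection".
- **Primary study parameter(s):** the quantity compared with the 10% limit is the "proportion of patients that received one or more seroma aspirations during the first 6 months post-operatively". Criteria a to c are not mentioned.
- **Abstract, Methods:** "The primary outcome is the proportion of patients undergoing one or more seroma aspirations", again without the criteria.
- **Primary objective:** omitting drains "does not lead to a higher incidence of seroma formation and seroma aspirations".

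Surgical treatment of a seroma appears only under Secondary outcome measures. Invasive interventions there comprise "every aspiration of clinically significant seroma, incision and drainage of abscess or infected seroma and/or operative debridement of the wound". The surgical site infection outcome in the same section lists aspiration for infection and surgical drainage as separate items.

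The Study design, Randomization and Blinding sections all say that blinding is not possible.

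**The concern.** The endpoint is defined by an act, needle aspiration, and not by the seroma problem that prompts the act. The protocol foresees a second route, surgical opening or debridement, and records it, but leaves it out of the quantity that decides the trial. A patient who goes straight to surgery and is never aspirated is scored like a patient who needed nothing.

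In a superiority trial, lost events often dilute a difference and so work against the claim. Here, events lost from the drain-free arm alone lower the estimated difference and support the claim. The choice between needle, surgery and waiting is made with the allocation known.

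The second matter is smaller. Whether an aspiration met criteria a to c is also judged unblinded. An aspiration that did not meet them is an event under the analysis sentence and a non-event under the definition.

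**Working it through.** **Inputs.** The Sample size section gives a 10% aspiration rate in each group, a 10-point limit, 80% power, 112 per group and 10% drop-out. The confidence level is not stated.

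**1. The plan's own figure.** n = (z_α + z_β)² × [p₁(1−p₁) + p₂(1−p₂)] / margin².
- One-sided 5%: (1.645 + 0.842)² × (0.09 + 0.09) / 0.10² gives 112 after rounding up, which matches. 112 / 0.90 = 124.4, so 125 per group and 250 in total, which also match.
- One-sided 2.5% gives 142, which does not match.

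The sample size arithmetic is not in question. One-sided 5% is used below because it reproduces the plan.

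**2. Who is a non-event.** Reading the outcome sections together:

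| Course within 6 months | Primary event? | Recorded as invasive intervention? |
|---|---|---|
| Aspiration meeting a to c | Yes | Yes |
| Aspiration, then incision | Yes, if the aspiration met a to c | Yes |
| Incision/drainage or debridement, never aspirated | No | Yes |
| Aspiration outside a to c | No by the definition; yes by the analysis sentence | Not as worded |

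**3. How many patients decide the result.** Upper limit = (p_free − p_drain) + 1.645 × √[p_free(1−p_free)/112 + p_drain(1−p_drain)/112], with 11/112 (9.82%) in the drain arm.
- 14 drain-free events: 2.68 + 1.645 × 4.20 = 9.59 points, pass.
- 15: 3.57 + 1.645 × 4.27 = 10.60 points, fail.
- 16: 4.46 + 1.645 × 4.34 = 11.60 points, fail.

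The Newcombe interval also allows at most 14. At one-sided 2.5% the maximum is 13 (Wald, 9.88 points) or 12 (Newcombe). At this boundary, two drain-free patients opened surgically and never aspirated would change 16 v 11 (fail) into 14 v 11 (pass).

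**4. Error rate in an assumed scenario.** Suppose the true rate of any seroma intervention is 10% with a drain and 20% without, exactly at the limit. Let s points of the drain-free events be opened without aspiration, and none in the drain arm. The chance of declaring non-inferiority is Φ[(0.10 − (0.10 − s))/SE − 1.645], where SE uses 0.10 and 0.20 − s with 112 per arm.

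| s (points) | 0 | 1 | 2 | 3 | 5 |
|---|---|---|---|---|---|
| One-sided 5% | 5.0% | 7.6% | 11.3% | 16.3% | 30.5% |
| One-sided 2.5% | 2.5% | 4.0% | 6.4% | 9.7% | 20.5% |

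For s = 2: SE = √[(0.09 + 0.1476)/112] = 0.0461, and Φ(0.434 − 1.645) = 11.3%. The values of s are assumptions; the documents supply none.

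**5. Power if surgical events are added.** With a common rate p in both arms and 112 per arm, power is Φ[0.10/√(2p(1−p)/112) − 1.645]: 80.2% at p = 10%, 77.2% at 11%, 74.5% at 12%, 71.9% at 13% and 67.4% at 15%. Holding 80% at p = 12% would need 131 per group before drop-out.

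**The case against.** The strongest case for the plan has five parts.

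- **The definition is fixed.** Only one section is headed as the primary outcome, and it presents a to c as the rule for deciding when to aspirate. If that rule is followed, both numerators are the same, and the shorter sentences read as shorthand. This largely stands. A reader might infer that the numerator is open and could be chosen once results are known; the text does not support that. What remains is a difference for aspirations outside a to c, because no sentence links the analysis to the definition.
- **Seroma formation in the objective is loose wording.** This stands. A reader might take it as a third endpoint, but the outcome, sample size and analysis sections all rest on aspiration alone, so it does not affect the numerator.
- **Surgery does not by itself make a patient a success.** This stands. Aspiration followed by incision still counts, and criterion c provides for aspirating infected seroma. Only patients never aspirated are lost.
- **The bias is hypothetical.** This stands as to size. It needs surgery without aspiration at a rate that differs by arm, and the trial expects comparable infection rates. The 16 v 11 example is a chosen borderline case; any binary non-inferiority test turns on one or two patients near its boundary.
- **The harm would be visible.** This stands in part. Invasive interventions are recorded from day 1 and surgical drainage feeds the infection outcome, but neither enters the non-inferiority decision.

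**Conclusion.** The point holds in limited form. As written, surgical drainage or debridement without any aspiration in 6 months is a non-event in the primary comparison. If it is more frequent without a drain, it favours non-inferiority; at equal frequency it does not shift the difference. Its likely size cannot be derived from the documents. The calculations show only sensitivity: about two patients at the boundary, or an error rate rising from 5% to 11% under an assumed 2-point shift in the drain-free arm alone.

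The definition and the analysis sentence also give different numerators for aspirations outside a to c, and for those only.

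A reader might conclude that the primary endpoint should become a composite. The documents do not support going that far. Aspiration is the trial's stated question, and the 10% rate and 10-point limit were set for it. A composite would change what is estimated and could lower power. Debridement is recorded in relation to seroma or wound healing, so restricting it to seroma would need a further unblinded judgement. A pre-specified sensitivity analysis meets the concern without those costs.

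**What to change.** 1. Keep aspiration as the primary endpoint. In Primary study parameter(s) and the abstract, refer to aspiration of clinically significant seroma as defined under Primary outcome measure.
2. Pre-specify two sensitivity analyses against the same 10-point limit:
   - (i) patients with at least one aspiration, incision and drainage of an abscess or infected seroma, or operative debridement, as already recorded under the secondary outcome;
   - (ii) patients with any aspiration, whether or not criteria a to c were met.
3. State that the non-inferiority conclusion will be reported together with the result of (i).

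**Cost:** wording and a little more analysis. Analysis (i) uses interventions already recorded, and the planned sample size for the primary endpoint is unchanged. Analysis (i) will have less than 80% power if its event rate exceeds 10%, so a wide interval there should be read as imprecision as well as a possible warning. Nothing in the treatment of patients changes.

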#### Secondary outcome measures

Assess:
Number of invasive interventions related to seroma or wound healing defined as: every aspiration of clinically significant seroma, incision and drainage of abscess or infected seroma and/or operative debridement of the wound.Surgical site infection (SSI) rate, defined as redness, pain, heat or swelling at the site of the incision or by the drainage of pus. Infection rate will be measured by A) the need for antibiotics, B) seroma aspiration due to infection or C) surgical drainage.Cosmesis assessed by the patient at every planned outpatient clinic visit. At these visits patients are asked to rate the cosmesis of the chest wall using a numeric rating scale (NRS) on a scale from 0 to 10.Quality of life measured using the SF-12 (Short Form) Health Survey. This is a 12-item questionnaire used to assess health related quality of life from the patient’s perspective. Two subscales are derived from the SF-12: the Physical Component Summary (PCS) and the Mental Component Summary (MCS) with a range from 0 to 100. A score of less than 50 means the patient scores lower than the general population and a score of more than 50 means the patient scores higher than the general population. Patients will be asked at baseline and at every postoperative planned outpatient clinic visit to fill in this questionnaire.The number of outpatient department visits, measured during the first 6 months postoperatively. This will be measured to see if patients have to come to the hospital more often due to seroma or seroma related complications.Wound pain and pain at the drain site measured by the patient using the NRS on a scale from 0 to 10 at the first postoperative outpatient clinic visit.

All outcome measures will be measured during the first 6 months postoperatively.

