### Follow-up

The follow-up period will be 6 months after mastectomy. Patients will visit the outpatient department for evaluation at 1 week, 6 weeks, 3 months and 6 months. See Fig. 2 for the participant timeline. Table 1 represents the time schedule of enrolment, interventions and assessments.

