**ASSESSMENTS:**							
***Baseline characteristics***	X	X					
***Clinical assessment seroma and complications***				X	X	X	X
***Invasive interventions***			X	X	X	X	X
***SSI***				X	X	X	X
***Cosmesis***				X	X	X	X
***Additional OPD visits***				X	X	X	X
***Wound pain***				X			

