#### Secondary study parameter(s)

The proportion of patients with a surgical site infection will be compared between groups using Pearson’s chi-squared test. Differences in the mean scores on the SF-12 and the NRS for pain and for cosmesis will be compared using the independent-samples t-test. Poisson regression will be used to compare the number of outpatient department visits, measured during the first 6 months post-operatively. All secondary parameters will be tested on the intention to treat sample, and are measured over the first 6 months after treatment.

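### The visit outcome counts only outpatient department visits, while its objective and stated purpose concern unplanned, seroma-related visits to the hospital by any route

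*Protocol article*

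**What the plan says.** All references are to the protocol article.

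- **Secondary objectives:** the trial will assess whether patients "develop more surgical site infections or require more unplanned visits to the hospital". No route of entry to the hospital is named.
- **Secondary outcome measures, definition:** "The number of outpatient department visits, measured during the first 6 months postoperatively".
- **Secondary outcome measures, purpose (the next sentence):** "This will be measured to see if patients have to come to the hospital more often due to seroma or seroma related complications".
- **Abstract, Methods:** the list of secondary outcomes ends with "cosmesis, pain and number of additional outpatient department visits".
- **Table 1, Assessments:** the row is "Additional OPD visits", marked at 1 week, 6 weeks, 3 months and 6 months.
- **Secondary study parameter(s):** "Poisson regression will be used to compare the number of outpatient department visits", on the intention-to-treat sample.
- **Follow-up:** "Patients will visit the outpatient department for evaluation at 1 week, 6 weeks, 3 months and 6 months", which makes four planned visits.

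Emergency-department attendances and readmissions are not mentioned anywhere, either to include or to exclude them.

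**The concern.** The objective and the stated purpose concern the hospital. The variable that is counted and analysed concerns one department of it. The narrower term appears in four places (abstract, outcome definition, Table 1, analysis), so it is not one loose phrase.

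Followed literally, a woman who comes to the emergency department with a painful seroma, or who is readmitted, adds nothing to the visit count for that contact. The count then answers its own objective only in part. The trial is meant to inform whether drains can be omitted, so a finding of no difference in visits may be taken as reassurance about hospital burden in general, when it covers clinic attendance only.

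**Working it through.** **Step 1. The wording side by side.**

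| Place | Where the contact occurs | Which contacts |
|---|---|---|
| Secondary objectives | hospital | unplanned |
| Outcome definition | outpatient department | no limit stated |
| Outcome purpose | hospital | due to seroma or its complications |
| Abstract, Methods | outpatient department | additional |
| Table 1 | outpatient department | additional |
| Secondary study parameter(s) | outpatient department | no limit stated |

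Two things vary: the route, and whether planned visits belong in the count.

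**Step 2. What one extra emergency or readmission contact contributes.** It adds 0 under every wording of the count. The patient's total depends on the second column of differences. Under the abstract and Table 1 it is 0 if she has no other extra clinic visit. Under the outcome definition and the analysis section it is 4 if she attends all four planned visits.

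**Step 3. What other outcomes capture.** Invasive interventions cover "every aspiration of clinically significant seroma, incision and drainage of abscess or infected seroma and/or operative debridement of the wound", with no limit on setting. An aspiration for clinically significant seroma also enters the primary outcome. Infection is measured by need for antibiotics, aspiration due to infection, or surgical drainage. Adverse events of grade 3 or higher are recorded for 6 months (Monitoring). None of these counts hospital contacts. An emergency assessment that leads to no procedure, no infection record and no grade 3 event appears nowhere. A readmission for antibiotics appears as an infection but not as a visit.

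**Step 4. Size, by illustration.** The plan gives no figure for this outcome, so there is none to reproduce. The input from the documents is n = 125 per arm (Sample size). The rates λ and the missed shares s are assumptions.

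- Observed rate per arm: m = λ(1 − s)
- Rate ratio: RR = m₁/m₀ (drain-free over drain)
- Standard error of ln RR: √[1/(n·m₀) + 1/(n·m₁)]
- Power, two-sided 5%: Φ(|ln RR|/SE − 1.96)

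With λ₀ = 0.2 (drain), λ₁ = 0.4 (drain-free) and nothing missed: SE = √(1/25 + 1/50) = 0.245; 0.693/0.245 = 2.83; power = Φ(0.87) = 0.81.

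| Missed, drain / drain-free | m₀, m₁ | Difference | RR | Power |
|---|---|---|---|---|
| 0% / 0% | 0.20, 0.40 | 0.20 | 2.00 | 0.81 |
| 10% / 10% | 0.18, 0.36 | 0.18 | 2.00 | 0.77 |
| 30% / 30% | 0.14, 0.28 | 0.14 | 2.00 | 0.66 |
| 10% / 30% | 0.18, 0.28 | 0.10 | 1.56 | 0.37 |
| 30% / 10% | 0.14, 0.36 | 0.22 | 2.57 | 0.92 |

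A second assumed pair, 0.5 and 0.75, shows the same pattern. RR is 1.50 with power 0.70 when nothing is missed. Equal loss of 10% to 30% keeps RR at 1.50 with power 0.65 to 0.55. Unequal loss gives 1.17 (10% / 30%) or 1.93 (30% / 10%).

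**Step 5. Planned visits in the count.** If the four planned visits are included and all attended, the first pair gives RR = (4 + 0.4)/(4 + 0.2) = 4.4/4.2 = 1.05 instead of 2.00. The mean difference stays at 0.20, because the planned visits cancel. The definition must therefore settle this along with the route.

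**The case against.** The strongest case on the other side has four parts.

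- **The article is condensed.** Which contact types the case report form counts is often left to the full protocol, which is not shown, and the exclusion is inferred from the term outpatient department. This stands as a caution: the full protocol may define the count more widely. It does not remove the point, because the article states an objective and a purpose that differ from the variable it defines and analyses.
- **The serious episodes are mostly captured elsewhere.** This largely stands. A reader might infer that the worst courses vanish from the trial, or that such a patient scores zero. The documents do not support either. Procedures and infections are counted whatever the setting, and under the outcome definition her planned clinic visits still count. What is lost is the contact as a contact.
- **The gap is the same in both arms.** This stands. A reader might infer that the outcome hides harm from omitting drains. Nothing in the documents shows that drain-free patients bypass the clinic more often. Equal loss leaves the rate ratio unchanged, and unequal loss could push it either way.
- **Clinic visits are a reasonable burden measure.** The Background names repeated outpatient visits as a consequence of seroma. That explains the choice but does not reconcile it with the objective, which lists unplanned hospital visits separately from interventions and infections.

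**Conclusion.** The mismatch is plain on the text: the counted variable is narrower than the objective and the stated purpose, which are therefore only partly answered. Equal loss in both arms costs precision and shrinks the absolute difference. In the illustration, power falls from 0.81 to between 0.77 and 0.66 and the difference from 0.20 to between 0.18 and 0.14 contacts per patient, with the rate ratio unchanged. Unequal loss would bias the ratio in either direction. These figures rest on assumed contact rates, assumed missed shares and a Poisson variance. The documents give no rates from which to size the effect, and no ground for claiming a direction. The point concerns one secondary outcome and leaves the primary non-inferiority conclusion untouched. It is worth correcting because the correction is cheap.

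**What to change.** Use one definition in the abstract, Secondary outcome measures, Table 1 and Secondary study parameter(s): the number of unplanned hospital contacts related to seroma or the wound within 6 months of surgery, by any route (outpatient department, emergency department or readmission), excluding the four planned visits listed under Follow-up. Count an emergency visit that ends in admission as one contact. Record the type, date and reason of each contact. Analyse the total and report the types descriptively.

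The cost is the wording, one field on the case report form and slightly more chart abstraction. Contacts at other hospitals will not be in the centre's own records, so patients should be asked about them at the planned visits.
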